#### Follow-up

▪ The first assessment will take place in the first week of life. The mother and the baby will be summoned to the Universidad de La Sabana Clinic and a nursing professional will perform it. This consultation aims to record the birth weight, the effectiveness of human lactation and feeding capacity and the need for hospitalization.▪ Monthly follow-up. This follow-up procedure will take place via monthly telephone calls with the mothers for 6 months, checking their adherence to human lactancy and, in the cases where breastfeeding has been suspended, inquiring about the reasons for this.

### Registration information

An electronic information collection instrument will be created and a paper record of the data collected for the study will also be kept. Periodically (every month), the research team will verify the information in the database with respect to the physical record. To reduce errors in information collection, double entry of information is performed.

The data will be kept in the research office of the Universidad de La Sabana Clinic and only the research group and regulatory personnel (INVIMA) have access to it if, for any reason, it should be required.

### Sample size

24 % babies in Colombia, received exclusive breastfeeding up to 5 months old (9). This was the baseline risk assumed for the sample size calculation [9]. No studies were found that comparing different strategies from SSC; so that estimate the sample size, information 2014 Cochrane meta-analysis was used [3], which compares SCC (regardless of the starting time) with nonintervention. In this meta-analysis, SSC increases exclusive human lactancy in babies of 3 − 6 months of age (RR 1.97, 95 % CI 1.37 to 2.83). With the information of exclusive breastfeeding for Colombia and the effect of SCC﻿, report in the meta-analysis, was estimated ﻿a sample size of 300 newborns. This sample was calculated, two tailed, for a type I error of 5 %, a type II error of 20 %, and an estimated loss rate of 30 %. Will be included 150 newborns per study group.

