**Methods/design:**

A randomized, blind clinical trial will be performed with full-term healthy newborns born at the Universidad de La Sabana Clinic. The blind trial participants will be those persons measuring the results and analyzing the data. The sample size will be calculated for a type I error of 5 %, a two-tailed type II error of 20 %, and an estimated percentage loss of 30 %; 150 infants will be included in each group. Randomization will be performed using permuted, size-6 blocks. Descriptive analysis will be conducted using central tendency and dispersion measurements. A bivariate analysis will be performed to determine which variables are associated with exclusive lactancy at 6 months. For continuous variables, Student’s *t* test will be used for independent samples, and the Wilcoxon rank sum test will be used if the assumptions of normality for the *t* tests are not fulfilled. The assumption of normality will be evaluated using the Shapiro-Wilk and Kolmogorov-Smirnov tests. Categorical variables in contingency tables will be constructed to assess the independence between variables using the chi-square test, or Fisher’s exact test when the assumption of the number of cases is not met by the values in the contingency tables multiplied by two. This will be calculated as a measurement of the effect of relative risk (RR) with confidence intervals; the adjusted measurements will be calculated using a multivariate regression Poisson model. Variables with significant results will be used in the bivariate analysis, and those with biological plausibility will be used for the adjustment. The analysis will be carried out for a two-tailed type I error level of 5 %. The Stata 11 program will be used for data analysis. An interim analysis will be performed upon the submission of half the expected events (106), setting limits for the early termination of the trial according to the method proposed by Pampallona and Tsiatis (1994). Intervention: There will be two SSC randomization groups: early versus immediate. After completing the neonatal adaptation process and based on the group assignment, the mother will be left with her newborn child in hospital accommodation. Prior to discharge, the Infant Breast-Feeding Assessment Tool (IBFAT) will be applied. Monitoring will initially be performed with a face-to-face assessment between 3 and 10 days of life, followed by monthly telephone calls for 6 months to verify lactation status.

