#### Outcomes

##### Primary outcome

Exclusive human lactancy for three or more months: exclusive human lactancy is defined as the time in months with human lactation as the only food source and without having received other liquids or solid foods (except drugs and/or vitamins).

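### The stated sample size inputs give 180 to 212 newborns, not 300; the stated power is understated for those inputs, and two of the inputs are proxies that should be labelled as such

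*Protocol article*

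**What the plan says.** The Sample size section lists every input. The control rate is the 24% of Colombian babies who "received exclusive breastfeeding up to 5 months old", and the section adds: "This was the baseline risk assumed for the sample size calculation". The effect is a relative risk of 1.97 (95% CI 1.37 to 2.83) for exclusive breastfeeding at 3 to 6 months. It comes from a meta-analysis "which compares SCC (regardless of the starting time) with nonintervention", used because the authors found no study comparing skin-to-skin strategies with each other. The error rates are stated as follows: "This sample was calculated, two tailed, for a type I error of 5 %, a type II error of 20 %, and an estimated loss rate", the loss being 30%.

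The conclusion is a total of 300: "Will be included 150 newborns per study group". The Abstract repeats it ("150 infants will be included in each group"), and the Randomization section also uses 300.

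The primary outcome is "Exclusive human lactancy for three or more months", and the Hypothesis section uses the same three-month threshold. Under Interventions, the control arm also receives skin-to-skin contact, started later.

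**The concern.** A sample size paragraph should let a reader get from its inputs to its total. Here all the inputs are printed and the total does not follow from them, so the printed size and the printed power cannot both be right.

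Two of the inputs also do not describe this trial directly. The baseline is for a later age than the endpoint, and the effect is for a different contrast. What is at stake is how the result will be read: the 80% statement is the only guide a reader has to which differences the trial could detect, and it is inaccurate for the stated effect and silent about smaller ones.

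**Working it through.** **Inputs, all from the Sample size section.** p1 = 0.24; p2 = 0.24 × 1.97 = 0.4728; difference d = 0.2328; two-sided 5% (z = 1.960); 80% power (z = 0.842); 30% loss; equal allocation. The average rate is 0.3564.

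**Step 1. Evaluable newborns per arm.** Write V = p1(1−p1) + p2(1−p2) = 0.1824 + 0.2493 = 0.4317, and P = 2 × 0.3564 × 0.6436 = 0.4588.

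- Unpooled: (1.960 + 0.842)² × V / d² = 62.5, so 63.
- Pooled: (1.960√P + 0.842√V)² / d² = 65.2, so 66.
- Continuity-corrected: (65.2/4) × [1 + √(1 + 4/(65.2 × d))]² = 73.6, so 74.

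Other methods stay in this range: arcsine gives 65, log relative risk 74, and Fisher's exact test about 74 (power 80.4%).

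**Step 2. Loss applied once, n / 0.7.**

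| Method | Evaluable per arm | Randomised per arm | Total |
|---|---|---|---|
| Unpooled | 63 | 90 | 180 |
| Pooled | 66 | 95 | 190 |
| Continuity-corrected | 74 | 106 | 212 |

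Multiplying by 1.3 instead gives smaller totals, 172 (pooled) to 193 (continuity-corrected). The plan's 300 is not reproduced: 300/212 = 1.42 and 300/180 = 1.67.

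**Step 3. How 300 might have arisen.** Applying the loss twice to the continuity-corrected figure gives 73.6/0.7/0.7 = 150.2 per arm. This fits, but it is an inference. Three other routes also land near 300: 95% power (296 to 309), two-sided 1% with continuity correction (303), and a relative risk of 1.75 (303). Each departs from a stated input. The article states no inflation for the interim analysis, and that inflation would have to be a factor of 1.42 to 1.67.

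**Step 4. Power of the planned trial at the stated effect.** Evaluable per arm = 150 × 0.7 = 105. Pooled-variance power is Φ[(√105 × 0.2328 − 1.960√P)/√V] = Φ(1.61) = 94.6%. With a continuity correction it is 92.8%.

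**Step 5. What 105 evaluable per arm can detect.** The documents give no 3-month baseline, so the rates above 24% are assumptions.

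| Baseline at 3 months | RR detectable with 80% power | Power at RR 1.5 | Power at RR 1.37 |
|---|---|---|---|
| 24% | 1.75 (42% in the other arm) | 47% | 30% |
| 30% | 1.63 (49%) | 61% | 39% |
| 40% | 1.48 (59%) | 83% | 58% |
| 50% | 1.38 (69%) | 97% | 78% |

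The 1.37 is the lower confidence limit of the cited relative risk; 1.5 is illustrative.

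**Step 6. Direction of the baseline mismatch.** Exclusivity that has ended does not resume, so if 24% is the share still exclusive at 5 months, the 3-month share in the same population is at least 24%. How much higher is not known. A constant hazard through 24% at 5 months gives 0.24^(3/5) = 42%. The Background gives an average exclusive duration of 1.8 months, and under the same hazard assumption that implies exp(−3/1.8) = 19% if it is a mean, or 0.5^(3/1.8) = 31% if it is a median. The document's own figures therefore support a range, not one value.

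**The case against.** The strongest reply is that the arithmetic error does no harm. For the printed effect the trial enrols more newborns than needed, and no error rate or analysis fails. That stands, and it sets the severity.

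The second reply is that the effect size is an openly declared substitute. The section says that no comparison of strategies was found and names the contrast from which the relative risk comes. That also stands: using the proxy is a disclosed assumption, not an error. What remains is that no reason is given for carrying it over to immediate versus early contact, and no figure shows the power if that effect is smaller.

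The third reply is that the baseline and the effect match each other, because 5 months lies within the 3-to-6-month window of the meta-analysis, and that a higher 3-month baseline would raise power at a fixed relative risk. Both statements are correct. The mismatch with the three-month endpoint remains, but it does not weaken the trial for a given relative risk.

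Three stronger readings are tempting, and the documents do not support them:

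- **That the trial is underpowered.** The arithmetic error runs the other way, and the documents contain no estimate of the immediate-versus-early effect from which a shortfall could be shown.
- **That the true baseline is about 42%, so that a relative risk of 1.97 would need an implausible 84%.** This rests on one assumed hazard and sets aside the 1.8-month average duration.
- **That the interim figure of 106 proves a double allowance for loss.** It equals 74/0.7 rounded up, but 150 × (0.24 + 0.4728) = 107 total expected events explains it about as well.

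**Conclusion.** The stated inputs give 180 to 212 newborns, not 300, under every standard formula tried with one allowance for loss. This does not depend on how 300 was obtained; a double allowance for loss is a plausible inference only. At the planned size, power for 24% versus 47.3% is about 93% to 95%, assuming exactly 30% loss in each arm and a two-proportion comparison without interim adjustment.

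The baseline time point is a real mismatch with the primary outcome. The relative risk of 1.97 is a disclosed proxy that needs clearer labelling. For effects smaller than the proxy, power falls below 80%: at a 24% baseline this happens below a relative risk of about 1.75. That describes what the design can detect and is not evidence that the trial will miss its effect. The point is a reporting correction to the stated size and power.

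**What to change.** Keep 300 and rewrite the Sample size paragraph, with the matching sentence in the Abstract:

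- Name the formula and apply the 30% loss once: 150 randomised and 105 evaluable per arm.
- Replace the 80% statement with about 95% power for 24% versus 47.3% (about 93% with a continuity correction), and add that 105 evaluable per arm has 80% power for a relative risk of about 1.75 at a 24% baseline.
- State that 24% refers to exclusivity up to 5 months, and give the detectable relative risk over an assumed 3-month range: about 1.75 at 24%, 1.63 at 30%, 1.48 at 40% and 1.38 at 50%.
- State that 1.97 is a proxy from contact versus none, say why it was accepted, and report the power for smaller effects: about 47% at a relative risk of 1.5 and 30% at 1.37, with a 24% baseline.

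The value 1.75 should be presented as what the design can detect, not as a new target, because it is solved from the sample size. If the authors had another reason for 300, such as a higher target power, they should state it instead. The cost is text only, with no change to enrolment, conduct or analysis.

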### Randomization

The 300 newborns will  be randomized using size-6 permuted blocks to ensure that there will be an equal number of participants in the control group and the intervention group. Once the mother signs the informed consent and the entry data for the study has been entered, the operation coordinator of the study will open the opaque envelope, the contents of which determines to which group the mother will be assigned and this information will be recorded immediately in the medical record. The coordinator will verify that the intervention to which the patient was assigned at birth is applied.

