### Study procedures

#### Prior to birth

▪ Prior to the start of the study, health personnel (nurses, pediatricians, and obstetricians) will undergo training regarding: SSC after birth in healthy newborns, human breastfeeding concepts (technical, definition of exclusive lactancy and its effective benefits and contraindications), the institutional human lactation protocol and management of the mothers with their newborn baby▪ The mothers who meet the entry criteria will be identified in the obstetrics and gynecology outpatient department at their prenatal appointment. An obstetric history will be conducted by the physician in order to identify risk factors or conditions that may contraindicate the study. Those mothers who meet the criteria for inclusion will be interviewed in order to explain the purpose of the study, its application and other events to be expected. Should they accept the offer of participation, they will sign an informed consent (Additional file 3) and their personal data, telephone number, and email address will be collected for follow-up▪ Those pregnant women who meet the inclusion criteria and sign an informed consent will be classified randomly using opaque envelopes allocated to the intervention or control group. Each envelope will be coded and assigned a study entry number. Prior to delivery, health professionals can determine what the intervention will be and prepare all their personnel to support the mother and child

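### A single published block size of 6 at one clinic with unmasked care lets anyone who tracks the sequence know about a quarter of allocations in advance

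*Protocol article*

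**What the plan says.** The abstract states: "Randomization will be performed using permuted, size-6 blocks". It adds that "150 infants will be included in each group" and that participants are "full-term healthy newborns born at the Universidad de La Sabana Clinic". The Randomization section repeats the block size and gives its purpose: allocation is "randomized using size-6 permuted blocks to ensure that there will be an equal number of participants" per arm. No stratification factor is mentioned.

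The same section describes the handling of envelopes. Opening comes only after consent and entry data. At that point "the operation coordinator of the study will open the opaque envelope". On what happens to the arm so revealed, the section says that "this information will be recorded immediately in the medical record". The coordinator then verifies that the assigned intervention is delivered.

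Under Prior to birth, mothers are identified at prenatal outpatient appointments and interviewed, and each envelope carries a code and a study entry number. That section also says: "Prior to delivery, health professionals can determine what the intervention will be". The Masking section blinds only those who measure the outcomes and those who analyse the data.

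Nothing in the article varies the block size, withholds it from staff or provides for central allocation.

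**The concern.** Allocation concealment has two parts: the current envelope must be unreadable, and its content must not be deducible from earlier ones. The plan secures the first by using opaque envelopes and opening them only after consent and entry data. It does not secure the second. With three places per arm in each block of 6, the rest of a block is determined once either arm has appeared three times. Because care is unmasked and each arm is written in the medical record, past allocations are visible at the clinic, and the block size is in print.

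If a person who can work out the next arm also influences whom to approach or when to enter her, mothers with stronger motivation to breastfeed could be placed preferentially in one arm. Motivation is plausibly related to the primary outcome, exclusive breastfeeding for three or more months, which is followed by telephone calls with the mother. The planned intention-to-treat analysis keeps each mother in her assigned arm, but cannot undo selection that took place at entry.

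**Working it through.** **Inputs.** Block size 6, fixed (abstract; Randomization). Allocation 1:1, 150 per group, 300 in total (abstract; Sample size). One clinic (abstract). One sequence is assumed, since no strata are stated.

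**The plan's own figure.** 300 / 6 = 50 complete blocks, and 50 × 3 = 150 per group. This reproduces the stated group size.

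**Certain allocations per block.** A block holds 3 places per arm, so there are C(6,3) = 20 equally likely orders. An allocation is certain when one arm's three places are already used.

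| Certain allocations in the block | Orders out of 20 |
|---|---|
| 1 | 12 |
| 2 | 6 |
| 3 | 2 |

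Mean = (12×1 + 6×2 + 2×3) / 20 = 30/20 = 1.5 per block, and 1.5/6 = 25%. The closed form for block size 2m, 2m/(m+1), gives 6/4 = 1.5 with m = 3. Over the trial, 50 × 1.5 = 75 of 300 are expected. The range is 50 (one per block) to 150 (three per block).

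**Best guess.** Always guess the arm with more places left, and toss a coin when they are equal. The probability of being right at positions 1 to 6 is:

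0.5 + 0.6 + 0.6 + 0.7 + 0.7 + 1.0 = 4.1 of 6, or 68.3%, against 50% by chance.

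A simulation of 1,000 sequences of 300 gave 24.98% certain and 68.3% guessed correctly.

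**With varied block sizes.** Assume sizes 4, 6 and 8 drawn with equal probability, and an observer who knows this set but not the order. The observer's probabilities are updated after every allocation, and an allocation counts as certain only when the next arm has probability 1.

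| Scheme | Certain | Best guess right |
|---|---|---|
| Fixed 6 | 25.0% | 68.3% |
| Mixed 4, 6, 8 | about 2% (2.1% to 2.4% across simulation runs) | about 68% |
| Mixed 4, 6 | about 5% | about 69% |

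Mixing therefore removes nearly all certainty but hardly changes the best guess.

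**Cost in balance.** If the mixed list is cut at 300 inside a block of 8, the arms can differ by at most 4.

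**The case against.** The strongest objection is that the link from predictability to bias is missing. The article does not say that the coordinator recruits. The coordinator acts after consent, the physician takes the obstetric history, and the interviewer is not named. Staff who learn the arm before delivery are preparing for a birth and are not described as following the sequence. The 25% applies only to a person who knows the block size and starting point, has logged every allocation in order, and can influence entry. All of this stands. A reader might infer that the people who enrol already know the allocations and that 75 mothers will be wrongly placed. The article supports neither inference: 75 is an expected number of predictable places, not of biased entries, and no effect on the relative risk can be derived from it.

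Two further points limit the consequence. All mothers must have expressed a wish to breastfeed, which narrows the range of motivation. Opening the envelope after consent also means that steering would require delaying an eligible mother or not approaching her. Neither removes the problem. Strength of motivation can still differ among willing mothers, and recruitment at prenatal visits leaves time to choose whom to approach and in what order.

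It is also fair to object that varied blocks barely change the best-guess rate. That is correct, so changing the block sizes is not enough by itself. A reader might claim a larger benefit by counting only allocations made at a running imbalance of four, which gives about 0.2% certain under mixed 4, 6 and 8. That count misses other histories that also determine the next arm. For an observer who knows the set of sizes, the figure is about 2%.

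Finally, a single sequence is inferred from silence on strata. Within strata, complete fixed blocks of 6 would still give 25% for someone following each stratum.

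**Conclusion.** The point holds as an avoidable weakness in allocation concealment. The fixed block size is a stated design choice, not a detail left to a fuller document, and its publication makes it usable by anyone at the clinic who follows the sequence. Such a person would know 25% of allocations with certainty (about 75 of 300 expected) and guess 68% correctly. The coordinator, as described, is in a position to track the sequence. Whether anyone in that position can influence entry is not stated, so the article shows predictability and a risk of selection bias, not bias itself. The figures assume 1:1 blocks filled in order and an observer with the full allocation history. The change is worth making because it costs almost nothing now, while selection at entry cannot be repaired after enrolment.

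**What to change.** Before recruitment opens (the article says that it has not):

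1. In the Randomization section, replace the fixed size with randomly varying block sizes, for example 4, 6 and 8. State that the sizes are not disclosed to the coordinator or clinical staff. Because size 6 is already published, the sizes actually used should not be published until enrolment is complete.
2. State that the record of past allocations is kept from whoever approaches and consents mothers, and say which role that is. If the coordinator opens the envelopes, the coordinator should not also recruit.

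The cost is a new list, a new set of envelopes and a sentence or two of text. The arms may end up differing by at most about four mothers, which has little consequence with 150 planned per group.

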##### Prior to discharge

Prior to discharge, the IBFAT instrument will be applied to the mother and her infant by the research monitor and/or operational coordinator.

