### Masking

As to the characteristics of the interventions under evaluation, those who measure the results and who will analyze the data will be blind. To ensure that the blind participant who measures the results will be someone other than the health professional applying SSC, that person will not be in the delivery room and will apply the study measurements to all newborns treated at the clinic without knowledge of whether or not they are study participants.

The person conducting the analysis will be given the database in which the variable that identifies whether the research subject belongs to the control group or the intervention group is found; this will then be coded and the code that identifies them will not be available to the analyst.

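### The article claims that everyone measuring outcomes is blind, but its stated procedures do not secure this for the telephone-reported primary outcome, the first-week visit or the IBFAT

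*Protocol article*

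**What the plan says.** - **Claim.** Under Masking, "those who measure the results and who will analyze the data will be blind". The abstract makes the same claim. Neither place excepts an outcome.
- **Means.** Masking gives two safeguards. The assessor is separate from the staff applying skin-to-skin contact, and "that person will not be in the delivery room". The assessor also "will apply the study measurements to all newborns treated at the clinic without knowledge of whether or not they are study participants".
- **Where the arm is filed.** Under Randomization, after consent and entry of baseline data, "the operation coordinator of the study will open the opaque envelope", and "this information will be recorded immediately in the medical record". The same section adds: "The coordinator will verify that the intervention to which the patient was assigned at birth is applied".
- **Who assesses before discharge.** Under Prior to discharge, "the IBFAT instrument will be applied to the mother and her infant by the research monitor and/or operational coordinator".
- **Who assesses later.** Under Follow-up, a nursing professional sees mother and baby at the clinic in the first week. Of the monthly follow-up the section says "This follow-up procedure will take place via monthly telephone calls with the mothers for 6 months". The caller is not identified.
- **Source of the primary outcome.** The primary outcome is exclusive lactation for at least three months. The section on instruments and assessment times takes its duration from the monthly telephone tracking, so it is what the mother reports.

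**The concern.** The article does more than assert blinding. It names a mechanism for achieving it and a place where allocation is filed. The mechanism does not fit how the primary outcome is collected, the filing place is one that a clinic assessor may be able to see, and one named assessor knows the arm by virtue of the job.

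The primary outcome is sensitive to this. Exclusivity is lost once any other liquid or food is given, so the answer can depend on how closely the caller asks and on what the mother believes is expected. If the person recording knows the arm, error can differ between arms. The mother knows her arm in any case. A report of the trial could then credit the primary outcome with more protection than the procedures give it.

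**Working it through.** The plan gives no figure on this point to reproduce. The check is mainly a comparison of the sections, followed by an illustration of scale.

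**Safeguards against assessments**

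| Assessment | Does not know who is enrolled | Absent from delivery room | Route to the arm |
|---|---|---|---|
| IBFAT before discharge | Possible in principle | Possible, but the coordinator may do it | Coordinator opens the envelope and verifies the arm |
| First-week visit (weight, feeding, hospitalization) | Doubtful: mother and baby are called in for it | Possible | Medical record, if the nurse can see it; the mother |
| Monthly calls (primary outcome) | Cannot operate: calls go to enrolled mothers | Possible | The mother; the record only if the caller has access |

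1. *Calls.* Telephone details are collected from consenting mothers for follow-up (Study procedures, Prior to birth). Anyone making these calls knows the mother is in the trial, so this safeguard fails for the primary outcome. The other safeguard can still apply. No further safeguard specific to the calls is stated.
2. *Record.* The arm is in the medical record from the opening of the envelope. The access limit under Registration information concerns study data held in the research office, not the medical record. No section restricts who may see the allocation entry.
3. *IBFAT.* Taking the operation coordinator of the Randomization section and the operational coordinator of the Prior to discharge section to be the same role, that person knows every arm and may score the IBFAT. Where that happens, the Masking claim is untrue for that outcome.

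**Scale, for illustration only**

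Inputs: rate 24 % in both arms (Sample size section, so true RR = 1); 150 per arm with 30 % loss, giving 150 × 0.70 = 105 evaluable per arm; two-sided 5 % test. Assumption: a share *m* of non-exclusive infants is recorded as exclusive in the immediate arm only, with no error in the control arm.

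Apparent rate = 0.24 + 0.76 × *m*; apparent RR = apparent rate / 0.24. The rejection probability uses a two-proportion normal approximation, with the pooled standard error for the critical value and the unpooled one for the observed difference.

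| *m* (assumed) | Apparent rate | Apparent RR | Chance of a significant result |
|---|---|---|---|
| 0 % | 24.0 % | 1.00 | 5.0 % |
| 2 % | 25.5 % | 1.06 | 5.8 % |
| 5 % | 27.8 % | 1.16 | 9.6 % |
| 10 % | 31.6 % | 1.32 | 23 % |
| 20 % | 39.2 % | 1.63 | 66 % |

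For *m* = 5 %: 0.24 + 0.76 × 0.05 = 0.278, and 0.278 / 0.24 = 1.16. For *m* = 10 %: 0.24 + 0.076 = 0.316, and 0.316 / 0.24 = 1.32.

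**The case against.** A reader might infer that the masking can work only in hospital, and that the visit and the calls are therefore unblinded. The documents do not support this, for three reasons.

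- Knowing that a mother is a participant is not knowing her arm. Absence from the delivery room can protect the visit nurse and the caller as well as a ward assessor.
- No section says that the nurse or the caller opens the medical record. The study keeps its own database and paper record, so follow-up data need not be taken from the chart. For the caller, who supplies the primary outcome, the record is not mentioned at all.
- In-hospital masking is not the sound part either, because the clearest contradiction, over the IBFAT assessor, lies there.

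Other points also carry weight. Staff are meant to know the arm before delivery so that they can prepare, so the entry has a purpose and cannot simply be withheld from the delivery team. The article never claims that mothers are blind, and their knowledge of the arm is inherent in the intervention. Both arms receive skin-to-skin contact and all mothers wished to breastfeed, so strongly one-sided misreporting is not self-evident. Additional file 2, which is not shown, may already fix the call questions, so the absence of a script cannot be alleged.

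These objections limit the point to blinding that is not secured, rather than blinding shown to be absent. They do not answer the failure of one stated safeguard for the calls, the unrestricted allocation entry, or the coordinator's two roles.

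**Conclusion.** The point stands in this limited form and should be dealt with before recruitment, which the article says has not opened. The unqualified blinding claim is not secured by the procedures given: one safeguard cannot work for the primary outcome, the medical-record entry is a possible route to unblinding at the first-week visit, and the section on pre-discharge assessment contradicts the Masking section if the coordinator scores the IBFAT.

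The size of any bias is unknown. The apparent RRs of 1.16 and 1.32 rest on assumed one-sided error rates of 5 % and 10 %, and they do not separate error by the assessor from error by the mother. Better masking of assessors can reduce only the former; the latter has to be acknowledged. The conclusion also assumes that the two coordinator titles denote one role and that no access restriction exists in a document not shown.

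**What to change.** 1. Keep the arm on a delivery-team sheet and in a restricted study log, or restrict access to the medical-record entry, so that the delivery team can see it and outcome assessors cannot.
2. Have the IBFAT, the first-week visit and the calls done by people with no part in allocation. Give them a contact list by study number without arm, and ask mothers not to disclose their group.
3. Reconcile the Prior to discharge, Randomization and Masking sections by removing the coordinator as a possible IBFAT assessor.
4. State in the abstract and the Masking section that assessors are masked to arm, but that the primary outcome and maternal satisfaction are reported by mothers who know their allocation.

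The cost is a little extra record handling and a less favourable blinding claim. The delivery team must keep ready access to the arm, so that the change does not lead to the wrong arm being delivered.
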